### Study design and randomization

2.1

This SOS-moral study is a randomized controlled trial with a multi-center design. The protocol was approved by the ethics committee of Beijing Anzhen Hospital (approval no. 2017059X) and has been registered at ClinicalTrials.gov (identifier: NCT 03372785).

Patients meeting the inclusion criteria will be categorized into two groups at a ratio of 1:1 according to a randomized digital table used to randomly assign patients to the CTO-PCI group (PCI of both the non-CTO artery and a concurrent CTO artery), or the non-CTO PCI group (PCI of only the non-CTO artery). The randomized digital form and interactive voice response mode will be applied to facilitate the randomization procedure. The randomization sequence will be produced and managed by an independent staff member. Before intervention, myocardial viability and cardiac function of patients will be evaluated using CMR. Cardiac function will be assessed using transthoracic echocardiography and CMR. The Seattle angina questionnaire (SAQ), Patient Health Questionnaire 9 and Generalized Anxiety Disorder Scale-7 will be used to evaluate patient QOL. Cardiac function, QQL, and MACE will be observed within 12 months of follow-up. A flow chart outlining the study design is depicted in Figure 1.

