#### Inclusion criteria

2.3.1

To meet inclusion criteria, patients should: be 18 to 80 years old; be diagnosed with single CTO concurrent with MVD detected using coronary angiography (at least one other major vessel should have exhibited no less than 75% stenosis); previously have been diagnosed with myocardial infarction, or suffer from myocardial necrosis in the territory of CTO artery determined by CMR; present with an LVEF above 35% determined using transthoracic echocardiography; present with CTO located in an epicardial coronary artery with a reference diameter of ≥ 2.5 mm; and comply with all the evaluations and follow-up protocols.

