#### Primary endpoint

2.6.1

The primary endpoint of this SOS-moral study will be difference in cardiac function observed between baseline and 1-year post-intervention, which will be determined by CMR and transthoracic echocardiography.

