### Statistical analysis

2.8

In the full analysis set, all randomized patients will be kept in the treatment group to which they were originally randomized. Moreover, patients without protocol deviation will be included in the per protocol set. Patients of the per protocol set will be included in baseline information analysis rather than in primary analysis if the CTO-PCI fails. Patients will not be included in the primary analysis if the MACEs occur.

Continuous variables normally distributed will be presented as means ± standard deviation, and student *t*-test will be used to make comparisons between two independent samples. Median and 4-quintile intervals will be used to express variables that are not normally distributed, and the Mann–Whitney *U*-test will be used to compare differences. Categorical variables will be presented as frequencies and percentages, and the differences between groups will be assessed using a chi-square test. Survival analysis will be performed using a Kaplan–Meier curve and Cox regression analysis. A 2-sided *P*-value < .05 will be considered statistically significant.

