## Conclusions

4

SOS-moral will sort myocardial viability before randomization to avoid the effect of viability of myocardial on cardiac function. Hence, the real benefits of CTO-PCI on cardiac function among these patients without 100% survival viable myocardial will be assessed. Furthermore, the present trial strictly recruits patients with MVD and concurrent CTO. SOS-moral will provide evidence for the value of CTO-PCI among these selected patients. Nevertheless, there remain several potential limitations in this study. First, SAQ may be affected by factors other than recanalization of CTO artery during the study period. Second, patients with high risk such as those with left main artery disease stenosis ≥50% and severe arrhythmia are not included. Patients with left main artery disease are not eligible because the PCI procedure needs to be individualized. Because cardiac function might be affected by the severe arrhythmia, those with severe arrhythmia will be excluded. Therefore, the outcomes are unable to include all patients at high risk. Third, in a limited study period, the study may be not powered to detected MACE differences between the two groups. Therefore, further studies including high-risk patients and with longer follow-up periods are needed in the future.

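### The only tests named for continuous outcomes are unadjusted, although baseline CMR LVEF and viability are collected: an avoidable loss of precision, not an error

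*Protocol article*

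**What the plan says.** All references are to the protocol article; no separate analysis plan is shown.

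- **Tests (Section 2.8).** For normally distributed continuous variables a Student t-test "will be used to make comparisons between two independent samples". For the rest, "Median and 4-quintile intervals will be used to express variables that are not normally distributed", and the Mann-Whitney U test "will be used to compare differences". The only regression named is Cox regression, for survival.
- **Primary endpoint (Section 2.6.1).** The "difference in cardiac function observed between baseline and 1-year post-intervention", by CMR and echocardiography. The Abstract names CMR only. The sample size (Section 2.7) is built on LVEF.
- **Baseline data (Section 2.1).** "Before intervention, myocardial viability and cardiac function of patients will be evaluated using CMR".
- **Allocation (Section 2.1).** Patients are "categorized into two groups at a ratio of 1:1 according to a randomized digital table". Nothing is said for or against stratification.
- **Viability.** Entry requires that patients "previously have been diagnosed with myocardial infarction, or suffer from myocardial necrosis in the territory of CTO artery determined by CMR" (Section 2.3.1). The Abstract and the Discussion exclude patients whose CTO territory is fully viable. The Conclusions state: "SOS-moral will sort myocardial viability before randomization to avoid the effect of viability of myocardial on cardiac function".

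**The concern.** Baseline LVEF predicts follow-up LVEF. A two-sample test on the change score assumes a slope of 1 on baseline. Whenever the true slope is lower, the test gives up precision and leaves part of any chance baseline difference in the contrast. A linear model with baseline as a covariate estimates that slope and recovers the loss at no cost in patients.

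Viability matters because of the article's own reasoning. The Introduction attributes conflicting earlier results partly to ignoring the state of the myocardium, and the Discussion reports that benefit was clearest in dysfunctional but viable segments. Viability is therefore a covariate the authors expect to be related to the outcome. It is collected, but no stated step balances it between arms or adjusts for it.

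The two-test rule raises a further point. The trial is sized on a difference in mean LVEF. If the primary comparison moved to Mann-Whitney U after the data were inspected, the reported result would no longer estimate that quantity.

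**Working it through.** **Inputs.** From Section 2.7: SD 9, boundary value 4 points, one-sided α 0.025, power 0.90, 216 evaluable, 240 randomised with 10% loss. Not given in the article, so assumed: the correlation r between baseline and 12-month LVEF (0.5 to 0.9), equal variances at both times, and 9 as the SD of the change.

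**Step 1: reproduce the plan's figure.** With 4 points as the detectable difference, n per arm = 2 × (1.960 + 1.282)² × 9² / 4² ≈ 106.4, rounded up to 107. The exact noncentral-t calculation gives 108 per arm, so 216 in total, and 216 / 0.90 = 240. Power with 108 per arm is 90.2% (exact t) or 90.4% (normal approximation). The stated size thus matches an unadjusted two-group test.

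**Step 2: adjust for baseline LVEF.** With equal variances, the variance of the change is 2σ²(1 − r) and the ANCOVA residual variance is σ²(1 − r²). Their ratio is (1 − r²) / [2(1 − r)] = (1 + r)/2, so the saving is (1 − r)/2.

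With 108 per arm, SE = SD × √(2/108) and the 95% half-width is 1.971 × SE. Power and the N for 90% power use the normal approximation. Exact-t powers are 90.2%, 96.4%, 94.1% and 91.6%, in the order of the rows.

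| Analysis | SD | Variance saving | 95% half-width | Power for 4 points | N for 90% power |
|---|---|---|---|---|---|
| t-test on change | 9.00 | – | 2.41 | 90.4% | 214 |
| ANCOVA, r = 0.5 | 7.79 | 25% | 2.09 | 96.5% | 160 |
| ANCOVA, r = 0.7 | 8.30 | 15% | 2.23 | 94.3% | 182 |
| ANCOVA, r = 0.9 | 8.77 | 5% | 2.35 | 91.8% | 204 |

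**Step 3: the other reading of SD 9.** Section 2.7 does not say whether 9 is the SD of LVEF or of its change. If it is the SD of LVEF at follow-up, the N for 90% power by change score versus ANCOVA is 214 v 160 (r = 0.5), 128 v 110 (0.7) and 44 v 42 (0.9). The percentage saving in variance is the same; the absolute figures differ.

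**Step 4: chance imbalance.** If baseline LVEF also has SD 9 (assumption), the 95% limit for a chance difference between arms is 1.96 × 9 × √(2/108) = 2.4 points. The change-score contrast then shifts by (1 − r) × 2.4, which is 1.2, 0.7 or 0.2 points at r = 0.5, 0.7 or 0.9. For a viability category held by half the patients (assumption), the limit is 1.96 × √(0.25 × 2/108) = 0.133, about 13 percentage points.

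**Step 5: viability.** The article gives no relation between a viability measure and LVEF change, so the added gain from adjusting for it cannot be computed.

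**The case against.** The strongest reply is that nothing here is wrong. An unadjusted t-test on a change score is unbiased on average under randomisation, keeps its type I error and delivers the planned power. The change score already uses the baseline, so at r = 0.9 the gain is slight. This stands, and it limits the point to efficiency.

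Second, the test rule is generic: Section 2.8 does not tie it to the primary endpoint, and an analysis plan that is not shown may name covariates. This stands in part. The rule is the only one given for continuous outcomes and the primary endpoint is continuous, so the comment concerns a stated method. If a fuller plan already specifies an adjusted model, the article's wording only needs to match it.

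Third, viability is handled at entry by excluding fully viable territories. That is a real design step and narrows the range. It does not equalise the remaining degree of necrosis between arms.

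Fourth, the Mann-Whitney sentence is conventional, and with about 108 per arm a comparison of means tolerates moderate non-normality. That is a reason to fix the mean difference in advance; it does not support leaving the choice to the data.

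Three stronger readings are tempting and unsupported. A reader might infer that allocation is unstratified, but Section 2.1 is silent and does not say so. A reader might infer that the unadjusted test leaves the trial short of power, but Step 1 gives 90.2% against the stated 90%. A reader might infer that the Conclusions make a promise about viability that is simply ignored, but the entry exclusion is at least part of what that sentence means.

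**Conclusion.** The point holds as an efficiency weakness. The article names only unadjusted tests for continuous outcomes while collecting the covariates that would sharpen the primary comparison, and it states neither stratification nor adjustment for the viability left after entry selection. The documents do not support calling the named test invalid or biased on average.

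The gain from baseline LVEF is a variance saving of 25% at r = 0.5, 15% at 0.7 and 5% at 0.9. Power moves from 90% to about 96%, 94% and 92%. The savings rest on an assumed correlation and equal variances at both times; the powers also require 9 to be the SD of change. No figure can be put on the viability term. The change is worth making because it is nearly free and settles in advance which quantity is estimated, but the trial does not depend on it.

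**What to change.** Replace the generic rule, for the primary endpoint only, with one prespecified analysis:

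- a linear model of 12-month CMR LVEF on randomised arm, baseline CMR LVEF, one prespecified baseline measure of CTO-territory viability (for example, extent of late enhancement) and centre;
- the adjusted mean difference with its 95% CI reported as the primary result, whatever a normality check shows;
- the t-test and Mann-Whitney U test on the change kept as sensitivity analyses.

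The primary measure must also be stated as CMR LVEF, since Section 2.6.1 refers to cardiac function by two imaging methods without naming one quantity. With that stated, the cost is analysis wording only: no extra patients, visits or scans, because the CMR covariates are already planned at baseline and centre is known.

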### Sample size calculation

2.7

PASS 15.0 will be utilized to calculate sample size. In the study, 226 individuals are predicted to be recruited in the trial. This sample size was calculated using the optimal efficiency test. The main purpose of this trial is to investigate the effect successfully opening concurrent CTO lesions on cardiac function in patients with MVD. LVEF has been taken into consideration for the calculation of sample size. Previous studies revealed a 6.5% mean difference between the two experimental groups and a 9% standard deviation with respect to LVEF. The optimal boundary value for LVEF was set to 4%.^[21]^ Two-hundred sixteen cases recruited to the study will allow for the use of a 1-tailed test with a significance level (α) set to 0.025, and power (1-β) of 0.90. Ultimately, it is estimated that 240 patients will be randomized, and a 10% loss is expected to occur throughout the 1-year follow-up period.

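### Section 2.7 words its 4-point LVEF figure as a superiority boundary but sizes the trial as if 4 points were the difference to detect against zero, and section 2.8 tests no boundary

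*Protocol article*

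**What the plan says.** Section 2.7 (Sample size calculation) describes its method with a term that has no standard meaning: "This sample size was calculated using the optimal efficiency test". The design inputs are then given: "Previous studies revealed a 6.5% mean difference between the two experimental groups and a 9% standard deviation with respect to LVEF". A further figure follows, in percent: "The optimal boundary value for LVEF was set to 4". The section does not say whether this 4 is the null value of the test, a margin, or the difference the trial should detect. It states that 216 cases "will allow for the use of a 1-tailed test with a significance level (α) set to 0.025", with "power (1-β) of 0.90", and that 240 will be randomised to allow for 10% loss.

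Section 2.8 (Statistical analysis) names Student's t-test for two independent samples, with Mann–Whitney for non-normal variables, and closes with "A 2-sided *P*-value < .05 will be considered statistically significant". It mentions neither a boundary nor a one-tailed test. Section 2.6.1 (Primary endpoint) defines the endpoint as a change in cardiac function and gives no hypothesis.

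**The concern.** An expected effect, a smaller separate boundary and a one-tailed 0.025 level are the usual ingredients of a superiority-by-margin test: reject only if the gain is shown to exceed 4 points. A t-test with no margin named is ordinarily a test of zero. Read this way, the two sections set different hurdles for the same comparison. A gain of, say, 4 points could be reported as an improvement under section 2.8 and as a missed boundary under section 2.7.

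The sample size points the other way. The 216 patients belong to a test of zero. Section 2.7 is therefore at odds with itself before it is compared with section 2.8, and a reader cannot tell from the article which hypothesis the trial was planned on or whether the stated 90% power applies to it.

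**Working it through.** **Inputs.** From section 2.7: expected difference 6.5, SD 9, the figure of 4, one-tailed α 0.025, power 0.90, 216 evaluable, 240 randomised, 10% loss. From section 2.1: 1:1 allocation, so 108 per arm. From section 2.8: t-test, two-sided 0.05. The SD of 9 is assumed to apply to the quantity compared between arms.

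**Step 1: reproduce 216.** Per arm, n = 2(z₀.₉₇₅ + z₀.₉₀)² SD² / d², where d is the distance between the true difference and the null value, and (1.960 + 1.2816)² = 10.51.

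- d = 4 (true 4, null 0): 2 × 10.51 × 81 / 16 = 106.4, so 107 per arm and 214 in total. The exact noncentral-t calculation gives 108 per arm, **216** in total. Then 216 / 0.90 = **240**. Both stated figures reproduce.
- d = 2.5 (true 6.5, null 4): 2 × 10.51 × 81 / 6.25 = 272.4, so 273 per arm and **546** in total (548 by noncentral t). Then 546 / 0.90 = 606.7, so 607 randomised.
- d = 6.5 (true 6.5, null 0): 82 in total (84 by noncentral t).

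Relaxing the boundary version does not rescue it: one-sided 0.05 gives 444, 80% power gives 408, and both together give 322. It would reach 216 only with an SD of about 5.7, not 9. The arithmetic for d = 4 would also serve a 4-point non-inferiority margin with no true difference, but that does not fit the aim of showing improvement or the 6.5-point expected effect.

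**Step 2: thresholds with 108 per arm.** SE = 9 × √(2/108) = 1.225, and t₀.₉₇₅ with 214 df = 1.971.

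- Null of 0: the smallest successful gain is 1.971 × 1.225 = 2.41 points.
- Null of 4: 4 + 2.41 = 6.41 points.

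A one-tailed 0.025 test and a two-sided 0.05 test have the same critical value in the direction of benefit. If both sections test zero, both thresholds are 2.41.

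**Step 3: power of the boundary test at 216.** (6.5 − 4) / 1.225 = 2.041; 2.041 − 1.960 = 0.081; Φ(0.081) = 0.53. With all 240 analysed it is 0.58.

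**Step 4: what follows if 4 is the null value.** Probability of success by true gain, from the noncentral t:

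| True gain | Null of 0 | Null of 4 | Difference |
|---|---|---|---|
| 4 | 90.2% | 2.5% | 88 points |
| 4.44 (pooled gain cited in the Discussion) | 95.0% | 5.5% | 90 points |
| 6.5 | over 99.9% | 52.9% | 47 points |

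The difference column is the share of trials in which the two rules disagree. It applies only on the boundary reading. On the other reading it is zero.

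**The case against.** The strongest reply is that there is no conflict of decision rules. Section 2.7 never says that 4 is the null value. The only quantitative evidence of what its authors computed is 216, and 216 is a test of zero sized for 4 points. Section 2.8 is then consistent with it. The two-sided sentence is also a general convention for every test in that section, and a formal hypothesis may stand in a full protocol or analysis plan that is not shown.

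Much of this stands. A reader might infer that the article fixes two different success rules and that they would disagree in 88% of trials at a true gain of 4 points. The documents do not support that as a settled fact, because it assumes the reading that the section's own sample size rules out. A reader might also infer that one-tailed against two-sided is a contradiction in itself. It is not, because the threshold for benefit is the same.

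What the reply does not remove is the mismatch inside section 2.7. If 4 is the detectable difference, calling it a boundary is wrong and the 6.5 plays no part in the calculation. If 4 is a boundary, the stated power is wrong. The objection is to what the article states, not to detail left to another document.

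**Conclusion.** The point holds in conditional form. Section 2.7 contradicts itself on the role of the 4 points, and nothing in the article resolves it.

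- **If 4 is the detectable difference** (the reading that 216 and 240 support): sections 2.7 and 2.8 agree on a threshold of about 2.4 points. The faults are the boundary wording and a 6.5-point figure that does not enter the calculation.
- **If 4 is a superiority boundary** (the reading that the wording suggests): section 2.8 never tests it, observed gains of about 2.4 to 6.4 points receive opposite verdicts, and power at a true gain of 6.5 is about 53%, not the stated 90%.

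These figures assume SD 9, 108 evaluable per arm, and LVEF change as the primary comparison. With all 240 analysed the window is about 2.3 to 6.3 points. The conflict in thresholds should not be presented as certain.

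**What to change.** State the primary null hypothesis once and use it in both sections.

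**Recommended.** The null is no difference between arms in 12-month LVEF change, tested at two-sided 0.05 and reported with a 95% confidence interval. In section 2.7:

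- replace the boundary sentence with *the difference the trial is sized to detect is 4 points (SD 9, 90% power, 216 evaluable)*;
- remove the 6.5 as a design input;
- give the level as two-sided 0.05, which leaves the threshold for benefit unchanged.

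A significant result should not be described as exceeding a 4-point boundary unless the lower 95% limit is above 4. For example, an observed gain of 4 points has a lower limit of 4 − 2.41 = 1.59. This route needs a few sentences and no extra patients. Its price is that a significant gain with a lower limit of 4 or less cannot be presented as meeting a 4-point boundary.

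**If a 4-point superiority boundary is really intended.** Section 2.8 must require the lower limit of the two-sided 95% interval (equivalently, the one-sided 97.5% bound) to exceed 4. The power must be restated as about 53% at 216 evaluable, or the size raised to about 546 evaluable (607 randomised at 10% loss). This is more than a wording change.

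Either choice should be made and recorded before outcome data are seen by arm.

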### Data collection, monitoring, and quality evaluation

2.9

Inclusion and exclusion criteria will be enforced strictly to minimize the potential for the inclusion of confounders. An experienced cardiovascular interventionist (CTO-PCI >50 cases/yr) has been designated to ensure that the success rate of CTO-PCI is above 80%. The number PCI performed within each of the centers participating in this study is least 3,000 cases. An expert committee has been established to ensure interventional safety and prevent study-associated complications. At least two senior experts in PCI (PCI >3000 cases per year) will assist to discern MACEs throughout the follow-up period. Two experienced specialists will acquire CMR images and collect data using specific equipment and software. Two independent investigators will be responsible for the creation of protocols and supervising follow up, and they will communicate with the enrolled participants throughout follow-up. The case report form will be completed by independent investigators. All data obtained will be documented in the database by two independent investigators according to guidelines governing data management. A special inspector will be responsible for tracking, monitoring and reviewing the research process, and it will not be possible to alter data at will. The database will be inactive after cross validation, followed by statistical analysis. The staff that perform analysis will be blinded to the intervention.

## Discussion

3

This trial aims to investigate the effect of CTO-PCI combined with non-CTO PCI on cardiac function in patients with MVD. Patients with MVD in a EuroCTO trial received non-CTO PCI before randomization; participants in the DECISION-CTO trial were not limited to those with MVD; the EXPLORE study recruited patients with STEMI. Consequently, a number of studies have investigated the clinical effects of successful CTO-PCI;^[6,10]^ however, there remains a lack of evidence from a randomized control trial, which can be sued to conclusively determine whether the success of opening concurrent CTO lesions improves cardiac function among patients presenting with MVD but not STEMI.

Early studies reported that successful recanalization CTO can both improve LVEF and ventricular wall movement assessed by CMR, and can improve QOL.^[22–25]^ An early meta-analysis found that successful recanalization of a CTO resulted in an overall improvement of 4.44% absolute LVEF points, reduced remodeling, and improved survival (OR: 0.52).^[26]^ However, the EXPLORE trial showed that in acute STEMI patients with concurrent CTO, CTO-PCI did not increase global LVEF or decrease LVEDV assessed by CMR 4-month post-PCI compared to patients receiving treatment in the non-CTO artery. Interestingly, a subgroup analysis of the EXPLORE trial showed that CTO-PCI in patients with a concurrent CTO in the LAD was associated with significantly higher LVEF levels after 4-month post-PCI compared with non-CTO PCI, suggesting that CTO-PCI may potentially benefit high-risk patients.^[19]^ According to Chung,^[27]^ the benefit of CTO-PCI is controversial with respect to cardiac function and survival among the MVD patients with concurrent CTO. This may partly be because myocardial viability affects the alteration of cardiac function produced by CTO-PCI. An in-depth analysis in the EXPLORE CMR study revealed that CTO-PCI was associated with the greater recovery of regional systolic function relative to baseline values 4-month post PCI in dysfunctional myocardial tissue supplied via CTO. The benefit was most evident in dysfunctional but viable segments (transmural extent of infarction <50%).^[28]^ The investigators opined that the benefit was probably attributable to the recovery of stunned myocardial tissue affected by the acute interruption of blood supply, as well as by the prevention of arrhythmia. Taken together, the data suggest that varying levels of myocardial viability in patients included in previous studies may be associated with reported variations in cardiac functioning observed after successful CTO-PCI treatments. Therefore, myocardial viability should be considered.

Previously, 128 patients were observed using CMR, and among the myocardial regions that corresponded to 149 CTO lesions, only 11.5% presented as transmural myocardial infarction. In fact, 58.6% of the myocardial segments showed no delayed enhancement.^[29]^ Differences in myocardial viability may contribute to the variable prognosis of CTO-PCI. A previous study including 32 CTO patients presenting with significant inducible perfusion deficits found that recanalization was associated with decreased ischemic burden, improved QOL, and reversed remodeling.^[23]^ The effect of CTO-PCI on cardiac function among patients with necrotic myocardial tissue in the territory supplied by the CTO combined with MVD requires further investigation. The present SOS-moral study excludes those patients with complete myocardial survival in the CTO artery territory. This distinction will facilitate the investigation of the effects of actively opening concurrent CTO lesion in MVD patients with necrotic myocardial tissue identified via CMR in the territory supplied by the CTO, aiming to provide reliable evidence for use in clinical practice.

CMR is an appropriate approach for the evaluation myocardial viability and cardiac function. The method is accurate, safe, and provides great spatial resolution as well as sensitivity.^[30]^ CMR has been used to assess myocardial viability throughout the previous decade. According to Cardona et al., CMR accurately detects myocardial viability in patients with reduced LVEF.^[17]^ We previously demonstrated that, using PET as gold standard, CMR has high consistency, sensitivity, and specificity for the detection of myocardial viability compared with PET in CTO patients.^[31]^ Therefore, in the SOS-moral trial, CMR will be used to evaluate both the amount of viable myocardial tissue and level of cardiac functioning.

